## Abstract

**Objective:**

The aim is to examine whether the addition of Virtual Reality (VR) meditation training to a standard 8-week Mindfulness-Based Health Care Program (MBHC-VR) results in a significantly increased improvement in occupational, mental health, and psychological functioning versus MBHC-only in university students.

**Materials and methods:**

A randomized controlled clinical trial with three arms (MBHC, MBHC-VR, Control Group), four assessment time points (pre-intervention, inter-session, post-intervention, and 3-month follow-up), and mixed methodology will be proposed. University students (undergraduate, master, or doctoral) interested in participating and who meet the inclusion/exclusion criteria will be included over two years. Data will be collected from different ad hoc questionnaires, several standardized tests, and an Ecological Momentary Assessment. We will use R software to carry out descriptive analyses (univariate and bivariate), multilevel modeling, and structural equation models to respond to the proposed objective. The qualitative analysis will be carried out using the MAXQDA program and the technique of focus groups.

**Discussion:**

It is expected that with the proposed intervention university students will learn to relate in a healthier way with their mental processes, so as to improve their occupational balance (OB) and their psychological well-being.

**Trial registration:**

ClinicalTrials.gov Identifier NCT05929430.

## Introduction

The mental health of university students have become a major public health concern [1, 2]. Between 29% and 37% of university students report elevated stress [3, 4], which can affect OB and contribute to the development of psychopathologies such as depression and anxiety disorders [5]. Psychopathological symptoms, including stress, anxiety, sleep problems, and depression, affect the university population around the world and are associated with poor academic performance and health risk behaviors, such as substance abuse, self-harm or suicide [6–8]. In 2016, the World Health Organization conducted a study with a sample of 5,750 university students from 21 countries and concluded that 20.3% met the criteria for a mental disorder according to the DSM-IV/CIDI [9]. This situation has worsened markedly after the COVID-19 pandemic according to a recent meta-analysis that showed a prevalence of 34% depression, 32% anxiety, and 33% sleep disorders in 1,441,828 university students from 29 countries [10, 11].

All these psychological symptoms influence OB, which is defined as an individual’s subjective perception of having an adequate number and variety of occupations in daily life [12]. A good OB is related to general mental health, satisfaction with life, and low stress levels, which makes it an important aspect to consider in clinical practice [13]. Empirical evidence showed that 62% of undergraduates feel dissatisfied with their daily routine [14], and usually have a moderate OB [15].

Taking into account the personal and social burden of mental health problems and occupational imbalance, a growing number of universities currently offer services and interventions aimed at these variables, including Mindfulness Based Programs (MBPs) [16]. Mindfulness is defined as the ability to pay attention to the present moment with interest, curiosity, and acceptance [17, 18]. The practice of mindfulness may change perspective, “decentering” or “re-perception”, so that the person can perceive internal experiences with great clarity [19, 20]. This shift in perspective facilitates self-regulation, clarification of values, cognitive, emotional, and behavioral flexibility, and the ability to deal with intense emotions objectively [17]. From conceptual and neural perspectives, research has identified four underlying mechanisms of action: 1) attention regulation: sustained attention to a selected object, shifting attention to the object every time a distraction occurs; 2) sensory awareness: attention to body sensations; 3) emotion regulation, modulating emotions without judgment; and 4) change in perspective on the self, moving to the role of the observer [21].

The practice of mindfulness meditation has shown important benefits in university students. A recent meta-analysis (n = 2201; 15 countries) that examined the effect of MBPs in university students showed beneficial results when comparing to a passive control group. The effect sizes were small-to-moderate for psychological well-being, anxiety and depression symptoms, perceived well-being, rumination, and mindfulness skills [22].

However, the low level of adherence to the MBPs in university students is considered an important limitation [23]. This highlights the need to identify innovative ways to improve home practice and adherence, such as the incorporation of virtual reality (VR) [24] to facilitate meditation practice. In fact, although further studies are required, virtual reality (VR) driven mindfulness training has demonstrated greater efficacy compared to traditional mindfulness methods [25], enhancing mental health and physical well-being. It has been proven to reduce anxiety [26, 27], pain [28], emotional exhaustion [29], fatigue [30], improve sleep quality [31] or help with smoking cessation [32], among others results. Virtual reality (VR) has the potential to enable users to encounter stimuli that might otherwise remain physically or cognitively out of reach, often due to avoidance or restricted imagination [33]. VR fosters a deep sense of immersion, carrying users into the core of these environments. A recent review of studies using mindfulness based on VR demonstrated that the more immersive VR (i.e., 3-dimentional head mounted VR screen) was more effective than the less immersive one (i.e., 2-dimentional computer generated screen). VR-based mindfulness practice usually contains images of natural environments, such as landscapes, rivers, mountains, oceans, forests, trees and rocks, with background music and audio guidance [25]. A recent clinical trial showed that MBPs with VR-assisted meditation practice resulted in 95.7% adherence which is between 16% to 30% higher than MBPs without VR [5].

For this reason, our RCT study will investigate the effects of a MBPs with versus without VR-assisted meditation in university students using quantitative and qualitative methods. For the quantitative approach, we will assess positive functioning, clinical measures and ecological momentary assessment (EMA) [34], to study the relationship between individual experiences, emotions, the social context, and behaviors. For the qualitative approach, we will conduct focus groups to explore potential psychological mechanisms of change associated with the implementation of standard MBPs without and with VR-assisted meditation.

The main objective of this study is to examine the differential effects of a Mindfulness-Based Health Care Program (MBHC) without versus with VR-assisted meditation (MBHC-VR) on OB and mental health (i.e. psychological distress) in university students. Our seven objectives are:

To compare the training effects on occupational indicators, such as occupational balance, eating habits, sleep and physical activity.To compare the training effects on mental health indicators, such as anxiety, depression, stress and burnout.To compare the training effects on psychological functioning, such as emotional regulation, acceptance, mindfulness-trait, self-compassion and life satisfaction.To test whether the training effects are maintained 3 months post-completion of MBHC.To identify potential mechanisms of change in MBHC vs MBHC-VR.To examine expectations of the participants before their participation in the program.To qualitatively explore the perceptions of the participants about the program and its effects after its completion.

### Hypotheses

We hypothesized that, compared to the waiting list control group, both MBHC and MBHC-VR will improve occupational indicators (Hypothesis 1), mental health (Hypothesis 2), and psychological functioning (Hypothesis 3). We expect that, compared to MBHC, MBHC-VR will have higher adherence to home practice [5], and result in greater magnitude of change in the occupational balance, mental health and psychological functioning variables (Hypothesis 4). Furthermore, we expect that improvements will be maintained at 3-months post-intervention completion [5] (Hypothesis 5). Finally, we predict that psychological functioning variables will act as mechanisms of change of occupational balance and mental health indicators in experimental vs control condition [35] (Hypothesis 6). All hypotheses will be tested in the post-training assessment, except for hypothesis 5, which will be tested in the follow-up.

## Material and methods

### Study design and setting

A randomized controlled clinical trial (RCT) with three arms and four assessment timepoints (i.e., pre-intervention, inter-session, post-intervention, and 3-month follow-up) using qualitative and quantitative methods. The three arms include an adapted MBHC [36], MBHC plus VR-assisted meditation (MBHC-VR), and a waiting list control group (WL). The study protocol has followed the SPIRIT guidelines [37] (S2 Appendix) and RCT was conducted following the recommendations of the Consolidated Standards of Reporting Trials (CONSORT) guidelines [38].

The clinical trial is based in the university of Miguel Hernández University of Elche which has a population of about 15000 students. This population is generally representative of university student populations in Spain. The duration of study participation for each student is five months in order to incorporate potential differences between the first and second semester of the academic year.

### Ethical consideration and declaration

The protocol of this clinical trial was approved by the Research Ethics and Integrity Committee of the Miguel Hernández University (DPC.ASP.01.22) and by Committee of Ethics of the Research with Medicines of the of the Elche General University Hospital (PI 132/2022) (S3 and S4 Appendices). Furthermore, the research was registered with ClinicalTrials.gov (ClinicalTrials.gov Identifier: NCT05929430) and will be performed in accordance with the Declaration of Helsinki as well as the Organic Law 3/2018 (December 5) on the Protection of Personal Data and Guarantee of Digital Rights. Data confidentiality is warranted during the whole research process (i.e., data collection, data cleaning and dissemination of research results).

Participation in the clinical trial will be voluntary, and participants will provide informed consent prior to their inclusion in the study. Data confidentiality will be protected during the research process (i.e., data collection, data cleaning, and dissemination of research results).

### Sample size estimation

G *Power (v. 3.1) was used to estimate the sample size needed to test hypotheses 1, 2, 3 and 5. A mixed model using treatment as a between-subjects factor (MBHC, MBHC-VR, and WL) and time as a within-subjects factor (pre, inter, post, and follow-up) will be tested. Interaction effect was powered. The sample size was estimated taking as a reference a small difference in perceived stress between MBHC with vs without VR-assisted meditation in university students [5]. With an alpha criterion of .05 and a small effect size (Cohen’s d^2^ = .08), to achieve a minimum of 80% power, a minimum sample size of 174 participants will be needed. Assuming an attrition rate, based on complete dropout of approximately 20% [5], the final sample needed will include at least 210 university students (i.e., 70 participants in each of three groups).

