P-values will be obtained through likelihood ratio tests comparing the full model (including the effect in question) with the model that excludes this effect. Z-values will be obtained to test the significance for fixed effects (estimates and standard errors data in the tables). Trends of the longitudinal data will be studied by testing the linear trend of the model for all the outcomes. Interaction effects between time and predictors will be performed. To estimate the magnitude of between-group differences at post-intervention and 3-month follow-up, effect sizes (Cohen’s *d*) will be calculated by dividing the differences in means by the pooled standard deviation (SD). The Cohen convention was used to interpret effect sizes, where effect sizes of 0.20 are categorized as small, effect sizes of 0.50 are classified as medium, and effect sizes greater than or equal to 0.80 are considered large.

Model comparison approach will follow Bliese and Ployhart [70] and Bliese [71] guidelines. The process begins by examining the nature of the outcome. To test the significance of person effects, a likelihood ratio test will be conducted to compare the null multilevel model (i.e., unconditional model) with a null single-level model, testing the null hypothesis that there are no group differences. The second step involves estimating the intraclass correlation coefficient (ICC) to calculate the between/within variation ratio. Model fit will be assessed using chi-square tests on the log-likelihood values and the Akaike’s information criterion (AIC) [72] relative goodness of fit index. According to the change in these fit indexes, the model with the last significant change will be chosen for each analysis.

MLM will be performed using the lme4 R package [73]. P-values of the lme4 outputs will be obtained by the lmerTest R package [74]. The Intraclass Correlation Coefficient (ICC) will be calculated by the sjstats R package [75]. Graphic data processing will be performed by the ggplot2 R package [76]. Visual inspection of q-q plots by the car R package [77] will reveal any deviations from homoscedasticity or normality in the dependent variables. In order to calculate multiple comparisons, Tukey/Bonferroni correction tests will be performed.

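### The 80% power claimed for Hypotheses 1-3 is the power of the omnibus group-by-time interaction, not of the two programme-versus-waiting-list contrasts that these hypotheses state

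*Protocol article*

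**What the plan says.** The section on sample size estimation states that G*Power "was used to estimate the sample size needed to test hypotheses 1, 2, 3 and 5". The model has three arms as the between-subjects factor and "time as a within-subjects factor (pre, inter, post, and follow-up) will be tested". It adds: "Interaction effect was powered". The effect size is taken from "a small difference in perceived stress between MBHC with vs without VR-assisted meditation in university students", and the inputs are given as "With an alpha criterion of .05 and a small effect size (Cohen’s d^2^ = .08". The result is 174 participants for at least 80% power, raised to 210 for dropout.

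The Hypotheses section states that, relative to the waiting list, "both MBHC and MBHC-VR will improve occupational indicators (Hypothesis 1), mental health (Hypothesis 2), and psychological functioning (Hypothesis 3". On timing it says: "All hypotheses will be tested in the post-training assessment, except for hypothesis 5, which will be tested in the follow-up".

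The quantitative data analysis plan fits a multilevel model with group, time and their interaction. On multiplicity it says: "In order to calculate multiple comparisons, Tukey/Bonferroni correction tests will be performed". It does not name the family of comparisons.

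**The concern.** The sample size section attaches one power figure to named hypotheses, but the test behind that figure is not the test the hypotheses describe. A 6-df interaction pools every arm difference over every occasion. Hypotheses 1-3 are two specific differences at one occasion: MBHC against waiting list and MBHC-VR against waiting list, both at post-training.

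Two things follow. The omnibus test can be significant when only one programme works, so its power says little about a claim concerning both. Each single contrast, and still more the pair, can also have much less power than the omnibus test. If a programme-versus-waiting-list contrast were not significant, readers would take it as a null result from a trial with 80% power for that question. The protocol does not show that it has such power.

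**Working it through.** **Reproducing 174.** The G*Power within-between interaction uses λ = N·f²·m/(1−ρ), df1 = (k−1)(m−1) and df2 = (N−k)(m−1). Here k = 3, m = 4 and alpha = .05. The protocol states no correlation, so ρ = 0.5 and f = 0.10 are assumed. At N = 174, λ = 174 × 0.01 × 4/0.5 = 13.92 on 6 and 513 df, and power is 80.4%. At N = 171 it is 79.6%. The printed d² = .08, read as f = √.08/2 = 0.141 with ρ = 0, gives the same λ (174 × 0.02 × 4 = 13.92). So 174 stands as an omnibus calculation, though its inputs are not unique.

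**From f to a post-training difference.** Let d be the full programme effect against waiting list at post-training, in SD units. Let t be the time pattern (pre, inter, post, follow-up) and g the arm pattern (WL, MBHC, MBHC-VR). Then f² = d²·Var(t)·Var(g), using population variances. For t = (0,1,1,1), Var(t) = 0.1875. For equal programmes, g = (0,1,1) and Var(g) = 2/9. So d = 0.10/√(0.1875 × 0.2222) = 0.490.

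**One programme only.** For g = (0,0,1), Var(g) is again 2/9. A d of 0.49 in one arm and zero in the other gives the same f = 0.10 and the same omnibus power, although Hypotheses 1-3 are then false.

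**Power of the contrasts.** The inputs are 58 per arm, complete data and baseline-to-post change. At ρ = 0.5 the change variance is 2(1−ρ) = 1. The noncentrality is d/√(2/58), for example 0.490/0.1857 = 2.64. Critical values on 171 df are 1.974 uncorrected and 2.364 for Tukey over three pairwise contrasts (assumed family). The two contrasts share a control arm, so they correlate 0.5.

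| Time pattern | d, equal effects | Each, Tukey | Both, Tukey | Both, uncorrected | Both, Tukey, MBHC at half effect |
|---|---|---|---|---|---|
| Sustained (0,1,1,1) | 0.49 | 61% | 45% | 62% | 19% |
| Gradual (0,.5,1,1) | 0.51 | 65% | 50% | 66% | 21% |
| From post only (0,0,1,1) | 0.42 | 47% | 30% | 46% | 13% |
| Peak at post (0,.5,1,.5) | 0.60 | 81% | 70% | 83% | 30% |

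Uncorrected, each contrast has 75-78% power in the first two rows. In the last column Var(g) = 1/6, and the MBHC-VR effect is 0.57, 0.59, 0.49 and 0.69 in row order.

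**Dependence on ρ.** If the omnibus power is held at 80%, f² is proportional to 1−ρ, so d² is too. The change-score variance is also proportional to 1−ρ, so ρ cancels. The table therefore holds at any ρ, while the implied d moves.

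**The printed effect size used directly.** Taking d = √.08 = 0.283 for each programme against waiting list at ρ = 0.5, the noncentrality is 0.283/0.1857 = 1.52. With Tukey, each contrast has 20% power and both have 9%.

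**Baseline-adjusted contrasts.** With a common baseline mean the variance factor is 1−ρ² = 0.75 at ρ = 0.5. The noncentralities are 0.490/√(0.75 × 2/58) = 3.05 (sustained) and 3.18 (gradual). Both succeed in 62-68% with Tukey, and in 77-81% when each is tested at .05. This gain does depend on ρ. At ρ = 0.7 the implied d is 0.38-0.40 and the variance factor 0.51. The noncentrality is then about 2.9-3.0, and joint power at .05 is about 70-75%.

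**The case against.** The strongest reply is that the documents do not fix the power of these contrasts. They give no programme-versus-waiting-list effect; the reference effect is a VR-versus-no-VR difference. They give no within-person correlation, comparison family or success rule. If d = 0.5 is kept and ρ = 0.7 assumed, baseline-adjusted joint power is 85-86%. This stands as an argument against any single headline figure. It does not rescue the 80%, because d = 0.5 at ρ = 0.7 is a larger effect than 174 implies at that correlation.

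Second, the word 'both' can be read as two component claims, which makes the single-contrast figures relevant. If both must succeed, no multiplicity correction is needed for that joint claim, so the uncorrected 62-66% is the fairer base figure. Both points stand, and both sets of figures are therefore shown.

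Third, a reader might infer that the trial will declare Hypotheses 1-3 from a significant omnibus interaction alone. The documents do not say so. The analysis plan also provides fixed-effect tests, multiple comparisons and between-group effect sizes at post-intervention and follow-up. The sample size section also discloses openly that the interaction was what it powered. What it leaves wrong is the assignment of that power to Hypotheses 1-3.

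**Conclusion.** The point holds as a mismatch between the powered test and the hypotheses. It is not an arithmetic error: 174 reproduces. The stated 80% belongs to a 6-df interaction and does not transfer to two post-training contrasts against the waiting list.

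The size of the gap depends on assumptions that the protocol leaves open. If the 80% omnibus power holds at 58 per arm with complete data, and Tukey covers three pairwise change contrasts, the probability that both succeed is 45-50% for equal sustained or gradual effects. It is about 30% if the effect appears only from post-training, 70% if it peaks there, and about 13-30% if MBHC has half the MBHC-VR effect. Reading the printed effect as d = 0.28 against waiting list gives 9%.

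A reader might infer that joint power simply is 45-50%, or that it falls short of 80% in every case. Neither is supported. The first rests on equal effects and a chosen time pattern. The second fails in the peak pattern, where both contrasts uncorrected reach 83% and a single contrast with Tukey about 81%.

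**What to change.** 1. In the sample size section, state that the 80% refers to the omnibus interaction only. For Hypotheses 1-3, report the power of each programme-versus-waiting-list contrast at post-training and the probability that both succeed. State the assumed d, correlation and correction.
2. In the quantitative data analysis plan, name these two contrasts as the tests that decide Hypotheses 1-3, preferably from a mixed model with a common baseline mean across arms. The common baseline is a gain in efficiency rather than the repair of an error.
3. State the success rule. If the claim is that both programmes work, test each contrast at .05, since requiring both already controls the error of that joint claim. Keep Tukey/Bonferroni for claims about a single programme.

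With all three, the equal sustained or gradual cases reach about 77-81% joint power at ρ = 0.5, and somewhat less at a higher correlation.

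The cost is wording in two sections and a different parameterisation of the same model, with no added participants or data. The downside is that the power the protocol can state for Hypotheses 1-3 becomes less favourable.

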**Sociodemographics**					
Age (in years)	X				ad hoc questionnaire
Sex	X				ad hoc questionnaire
Education level	X				ad hoc questionnaire
Marital status	X				ad hoc questionnaire
Work status	X				ad hoc questionnaire
Experience in mindfulness	X				ad hoc questionnaire

Abbreviations: OBQ-E Occupational Balance Questionnaire; DASS-21, Anxiety, depression and stress scale; MBI-SS, Maslach Burnout Inventory-Student Survey Questionnaire; DERS, Emotional Regulation Difficulties Scale; FFMQ-SF, The Five Facets of Mindfulness Questionnaire short FORM; SCS-SF, Self-Compassion Scale short form; SLS, Life Satisfaction Scale; AAQ-II, Acceptance and Action Questionnaire II; M-C SDS, Marlowe-Crowne Social Desirability Scale short form; Physical Activity Questionnaire short form (IPAQ-SF); Insomnia Severity Index (ISI); Plymouth Sensory Imagery Questionnaire (Psi-Q). ^a^ Inter-session measured with the Ecological Momentary Assessment (EMA).

*Main outcomes*. *Occupational Balance Questionnaire* (OBQ) [44] is a 13-item tool scored on a 6-point Likert-type response scale, ranging from 0 (strongly disagree) to 5 (strongly agree), with a total score ranging from 0 to 65, where a higher score indicates greater OB. The internal consistency of this instrument is 0.87.

*Depression*, *Anxiety and Stress Scale* (DASS-21) [45] measure psychological distress with 7 items for each subscale: depression, anxiety and stress. Participants rate the degree to which each statement has happened to them in the past week on a scale from 0 (has not happened to me) to 3 (has happened to me a lot or most of the time). The internal consistency of this assessment tool is 0.90.

Academic stress will be measured using the *SISCO Inventory* [46] which consists of 31 items distributed into: 1 filter item (yes-no), 1 item on a Likert-type scale from 1 (a little) to 5 (a lot), 8 items on a Likert-type scale from 1 (never) to 5 (always) that allow identifying stressful stimuli, 15 items on a Likert-type scale from 1 (never) to 5 (always) that allow identifying stressful stimuli divided into physical, psychological and behavioural reactions, and 6 items on a Likert-type scale from 1 (never) to 5 (always) allowing to identify the frequency of use of coping strategies. Its internal consistency is 0.90.

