### Data analysis

#### Quantitative data analysis plan

The data analysis plan will be conducted following four steps. R Software [66] will be used for all data cleaning and statistical tests with a significance level of alpha < .05.

*Data preprocessing*. Demographics and clinical records will be described at baseline by means of frequencies (percentages) or means (SD). Independent *t*-test for continuous data and chi-square test (*χ*^2^) for categorical data will be conducted to confirm that there were no demographic or clinical differences between groups at baseline. Following the CONSORT guidelines [38], Intention-To-Treat analysis will be performed using Maximum Likelihood estimation via Expectation Maximization imputation [67]. The procedure suggested by Hair et al [68] will be followed to handle missing data: 1) the types of missing data and percentage of missing will be analyzed to ensure that none exceed the recommended thresholds; 2) Little’s MCAR (Missing Completely At Random) test will be used to assess whether the missing data is completely random; and 3) sensitivity analysis will be performed to determine the impact of missing data on the results of a study, comparing the main outcomes between completers and imputed values.

*Multilevel Modelling (MLM)*. First, efficacy of MBHC and MBHC-VR compared to WL control condition will be analyzed by using MLM. Multilevel analysis enables the control of variance associated with random factors without the need for data aggregation. Variance across participants, instructor of each group, and subgroup of delivery (i.e., edition) will be modeled as random effects. Group (i.e., MBHC, MBHC-VR, and WL) and time (i.e., pre-intervention, inter-session, post-intervention, and 3-month follow-up) will be modeled as fixed effects. Analyses will be conducted via restricted maximum likelihood estimation (REML), which provides a less biased estimate of variance components with small sample sizes [69]. The group x time interaction will be used to study the trajectories of each group throughout the intervention and to determine whether the between-group differences are maintained over time.

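### The sample size and the mixed model assume four time levels, but Table 1 gives five of the six main outcomes only three, and stress an inter-session value only as a daily EMA item.

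*Protocol article*

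**What the plan says.** Under Sample size estimation, the design behind the calculation has "treatment as a between-subjects factor (MBHC, MBHC-VR, and WL") and "time as a within-subjects factor (pre, inter, post, and follow-up) will be tested". The article adds "Interaction effect was powered". The inputs given are "With an alpha criterion of .05 and a small effect size", printed as "small effect size (Cohen’s d^2^ = .08"), and the result is "to achieve a minimum of 80% power, a minimum sample size of 174 participants will be needed". Allowing for about 20% dropout, the target becomes 210, or 70 per arm. The effect size is referred to perceived stress. G*Power is named as the software, but the correlation among repeated measures and the sphericity correction are not given.

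The multilevel modelling part of the Quantitative data analysis plan repeats the factor: "time (i.e., pre-intervention, inter-session, post-intervention, and 3-month follow-up) will be modeled as fixed effects". The group by time interaction is the test of interest, and a linear trend is planned for all outcomes.

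Table 1 marks occupational balance, anxiety, depression, academic stress and burnout at pre-intervention, post-intervention and 3-month follow-up only. Stress is also marked at inter-session, with DASS-21 and EMA as its methods. The table footnote says "Inter-session measured with the Ecological Momentary Assessment (EMA"). Under Measures, the EMA is sent once a day throughout the six weeks. Stress in Table 2 is a single question about the present moment, answered on a 0-10 visual analogue scale.

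**The concern.** The time factor is fixed in two places and the measurement schedule contradicts it in both. An analyst who follows the model as written finds an empty level for five main outcomes, including occupational balance, which the main objective names. The analyst must then decide, with data in hand, whether to drop the level or fill it from the EMA. For stress that choice could change the result, because an EMA item and a DASS-21 subscale differ in scale, recall period and frequency.

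The same extra occasion enters the sample size. In a within-between interaction calculation, each added measurement raises the noncentrality. The stated 80% is therefore tied to a design that no main-outcome questionnaire has.

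**Working it through.** **Schedule against model.**

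| Main outcome | Pre | Inter | Post | 3 months |
|---|---|---|---|---|
| Occupational balance, anxiety, depression, academic stress, burnout | yes | none | yes | yes |
| Stress, DASS-21 (7 items scored 0-3, past week) | yes | none | yes | yes |
| Stress, EMA (1 item, 0-10, right now) | unclear | daily, 6 × 7 = 42 requests | unclear | unclear |

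With three groups, an inter-session level adds one time coefficient and two group by time coefficients. For the five outcomes in the first row no observation informs them, so they are not estimable.

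**Inputs for power.** From Sample size estimation: k = 3 groups, m = 4 measurements, alpha 0.05, N = 174, d² = .08. Assumed, because not stated: sphericity ε = 1, and either f = 0.10 with correlation ρ = 0.5, or the printed d² with ρ = 0.

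**Formula** (repeated-measures ANOVA, within-between interaction):
- λ = f² · N · m · ε / (1 − ρ)
- df1 = (k − 1)(m − 1), df2 = (N − k)(m − 1)
- power = P(noncentral F(df1, df2, λ) > the 95th percentile of central F)

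**Step 1: reproduce 174 with m = 4.**
- f = 0.10, ρ = 0.5: λ = 0.01 × 174 × 4 / 0.5 = 13.92; df = 6 and 513; power 0.804. The smallest N is 173, or 174 with equal arms.
- d² = .08: f = √.08 / 2 = 0.1414, f² = 0.02. With ρ = 0, λ = 0.02 × 174 × 4 / 1 = 13.92, so power is again 0.804.

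Both settings return the stated figure with four measurements.

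**Step 2: same f and ρ with m = 3.**
- N = 174: λ = 0.01 × 174 × 3 / 0.5 = 10.44; df = 4 and 342; power 0.730.
- N = 168, that is 210 × 0.80: λ = 10.08; df = 4 and 330; power 0.713.
- N = 210 with no loss: power 0.819.
- 80% power needs 202, or 204 with equal arms (power 0.806 at 204).

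The d² = .08, ρ = 0 setting gives the same λ and hence the same powers. More generally, any pair of f and ρ that gives exactly 80% at N = 174 with m = 4 gives 0.726 with m = 3, because λ falls by the factor 3/4. At 168 the four-measurement calculation gives 0.788, so most of the drop to 0.713 comes from the lost occasion and not from the dropout arithmetic.

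**Step 3: hold the means constant instead of f.** f is defined over the occasions included, so removing one can change it. Take a pattern of group differences at pre, inter, post and follow-up, scale it so that m = 4 gives λ = 13.92, then delete the inter-session value. λ is multiplied by the ratio of centred sums of squares. For 0, 0, 1, 1 the ratio is (2/3) / 1 = 0.667.

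| Pattern | λ ratio | Power, N = 174 | Power, N = 168 |
|---|---|---|---|
| 0, 0, 1, 1 | 0.667 | 0.672 | 0.654 |
| 0, 1, 1, 1 | 0.889 | 0.810 | 0.794 |
| 0, .5, 1, 1 | 0.970 | 0.847 | 0.832 |
| 0, .5, 1, 0 | 0.970 | 0.847 | 0.832 |
| 0, .5, 1, .5 | 1.000 | 0.859 | 0.845 |

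**The case against.** Four points can be made for the plan.

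- **The power loss is not established as a fact.** f = 0.10 is nowhere in the article, nor are ρ and ε. The setting that returns 174 is not unique, and four of the five mean patterns above stay over 80% at N = 174. With f = 0.10 and m = 3, ρ = 0.6 would give 0.833 and ρ = 0.7 would give 0.931, although neither reproduces 174. This stands. A reader might infer that the trial's true power is 73%, and the document does not support that.
- **Stress, the variable behind the effect size, is marked at all four occasions.** Measures also lists stress at baseline as DASS-21 and EMA, and says the post-intervention tools are those of baseline. The EMA item may therefore exist on one scale at pre, inter and post. The Table 1 footnote, which equates EMA with inter-session, points the other way. The ambiguity stands, but it does nothing for the other five outcomes. A reader might also infer that EMA and DASS-21 scores will be stacked as one response. Nothing in the article says so; the plan simply gives no rule.
- **The model can be fitted.** A reader might conclude that the analysis is unworkable. It is not: on three observed levels the same mixed model runs without redesign. Only the inter-session terms fail.
- **An article may list the study-wide timepoints once and leave outcome-specific levels to the full plan.** That is reasonable for the model sentence alone. It does not explain the sample size, where the four levels are an input to the calculation and the stated 174 reproduces only when they are counted.

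**Conclusion.** The contradiction is certain: a four-level time factor is specified for the power and for the model, while five of the six main outcomes have three levels. Stress has an inter-session value only as a daily item on another scale. The inter-session terms cannot be estimated for those five outcomes, and the stated 174 is a four-measurement figure.

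The effect on power is conditional. Under the apparent settings, with f and ρ held fixed and ε = 1, three measurements give about 73% at 174 evaluable participants and 71% at 168. If the mean pattern is held fixed instead, the range at 174 is about 67% to 86%, so the true power may lie on either side of 80%. What can be said firmly is that the 80% claim is unsupported for the questionnaire outcomes as scheduled.

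**What to change.** 1. In the multilevel modelling section, define time as pre-intervention, post-intervention and 3-month follow-up for every questionnaire outcome.
2. Analyse EMA items in a separate daily-level model over the six weeks. State that EMA and questionnaire scores are not combined in one response, and say which stress measure is the main outcome.
3. State in Measures and Table 1 whether the EMA items are also collected at baseline, post-intervention and follow-up.
4. Restate the power for three measurements, giving f, ρ and ε. Under the apparent settings this reads as about 73% at 174 evaluable participants.

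The cost is wording and a less favourable power statement. No new data and no further participants are needed. Restoring 80% under the apparent settings would be a different matter: 204 evaluable participants, or 204 / 0.80 = 255 enrolled against the planned 210. That is not proposed here. The changes should be made before any outcome data are analysed.
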